## 1.5 End-points

### 1.5.1 Primary

The primary endpoints are immunogenicity and safety as defined below.

The primary immunogenicity parameter will be the presence of CD8/CD4+ T cell responses defined according to internationally agreed criteria for evaluation of IFN $\gamma$  ELISPOT assays (see section 8),

- in response to *env plus* at least one of the *gag, pol, nef* peptide pools
- at weeks 26 or 28

The primary safety parameters will be graded according to appendix 4, and are:

- Grade 3 or above local adverse event (pain, cutaneous reactions including induration)
- Grade 3 or above systemic adverse event (temperature, chills, headache, nausea, vomiting, malaise, and myalgia)
- Grade 3 or above other clinical or laboratory adverse event confirmed at examination or on repeat testing respectively.
- Any event attributable to vaccine leading to discontinuation of the immunisation regimen.

Note of clarification 8th Nov 2006: This will capture all Serious Adverse Events (SAE) as defined by ICH GCP as well as other grade 3 and 4 events that do not meet the criteria of an ICH GCP SAE.

Data on local and systemic events listed above will be solicited with specific questions or using a diary card for a minimum of 7 days following each immunisation. Data on other clinical events and laboratory events will be collected with an open question at each visit and through routine scheduled investigations respectively.

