## **4 Assessments**

### **4.1 Safety assessments**

#### **4.1.1 Local adverse events**

Pain in the muscle injected will be graded by the participant according to the criteria in appendix 4 as mild (1) moderate (2), severe (3) or extreme (4) and recorded in the appropriate case record form or once the participant has left clinic, in the diary card.

Redness will be recorded as the maximum diameter and expressed as a proportion of the arm or thigh circumference and graded on this criteria and the presence of symptoms according to appendix 4. Arm circumference will be measured at screening at the point one third of the way down from the acromio-clavicular joint towards the elbow joint of the non-dominant arm, and thigh circumference half way between the iliac promontory and the patella. Participants will be asked to record the maximum diameter in the diary card, as well as the presence of any itching or other discomfort and any medication taken for relief of symptoms.

Blistering (vesiculation) or ulceration will be graded according to size, depth, time to healing and character of blisters (blood-filled).

The presence of induration (hardened swelling) following intramuscular injection will be considered grade 3 if considered by the clinician to have arisen from a pathological process within the muscle. Induration considered in the judgement of the clinician to result from product leaking into the intradermal or subcutaneous layers will be graded according to the intradermal parameters in the toxicity table (Appendix 4). Soft swelling local to the injection site is not considered induration and should be graded according to the soft swelling parameters in the toxicity table (Appendix 4).

Clinical staff will complete the case record form following each immunisation. Completed case record forms and the diary cards will be sent to the data coordination centres to be recorded on the database. In the event that there are two observations on the same day, those confirmed at a visit will take precedence over diary card observations in the analysis.

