| Pain at injection site                          | Mild, no Rx required or analgesics for mild-moderate pain                                                                          | Moderate requiring regular analgesics for mild-moderate pain or occasional analgesics for moderate-severe pain                                                                                                                                    | Severe, repeated analgesics for moderate-sever pain                                                                                                                                                           | Hospitalisation                                                                                         |
| Fever
Oral>12 hours                          | 37.7 - 38.9°C
(100.0 – 101.5°F)                                                                                                 | 39.0 – 39.7°C
(101.6 – 102.9°F)
OR max temp of 103°F                                                                                                                                                                                        | 39.8 – 40.5°C
(103 - 105°F)
OR max temp of 103.5°F                                                                                                                                                      | >40.5°C (105°F)
OR max temp of >105°F                                                                |
| Headache                                        | Mild, no Rx req, OR or analgesics for mild-moderate pain                                                                           | Mod requiring regular analgesics for mild-moderate pain or occasional analgesics for moderate-severe pain                                                                                                                                         | Severe; intractable; OR requiring repeated analgesics for moderate-severe pain                                                                                                                                | Requiring hospitalisation, or associated with neurological, respiratory or cardiovascular abnormalities |

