**Guide for grade of local reactions**

|                                                                        | Grade 1
mild                                       | Grade 2
moderate                      | Grade 3
severe                | Grade 4
Extreme |
|------------------------------------------------------------------------|---------------------------------------------------------------|--------------------------------------------------|------------------------------------------|----------------------------|
| Pain in injected muscle (including ache) NOT discomfort in skin | No treatment or responds to paracetamol like treatment | Regular paracetamol like treatment needed | Regular strong painkillers needed | Hospitalisation     |
| Itching or irritation in the skin at the site of injection      | No treatment or responds to paracetamol like treatment | Regular paracetamol like treatment needed | Regular strong painkillers needed | Hospitalisation     |

| Local Symptoms – please put in grade, including 0 if no symptoms and measure maximum width of skin lesion in cm |        |       |       |       |       |       |       |       |       |       |       |       |       |       |       |       |
|------------------------------------------------------------------------------------------------------------------------|--------|-------|-------|-------|-------|-------|-------|-------|-------|-------|-------|-------|-------|-------|-------|-------|
|                                                                                                                        | 12 hrs |       | Day 1 |       | Day 2 |       | Day 3 |       | Day 4 |       | Day 5 |       | Day 6 |       | Day 7 |       |
|                                                                                                                        | left   | right | left  | right | left  | right | left  | right | left  | right | left  | right | left  | right | left  | right |
| Pain at injection site                                                                                          |        |       |       |       |       |       |       |       |       |       |       |       |       |       |       |       |

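### Injection-site pain is graded by three definitions that do not match, so the same severe pain can be recorded as grade 1 or grade 3, and that decides entry into the primary safety endpoint.

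*Protocol*

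**What the plan says.** Section 1.5.1 makes "Grade 3 or above local adverse event (pain, cutaneous reactions including induration") a component of primary safety, graded by Appendix 4. Section 8.2 compares the resulting proportions between groups with Fisher's exact test. Section 7.7.2 counts participants with grade 3 or 4 events attributed to one product. At three or more, recruitment and immunisation with that product are held for an unblinded review by the DSMC.

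Three places say how pain is graded:

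- **Section 4.1.1.** The participant grades the pain "according to the criteria in appendix 4 as mild (1) moderate (2), severe (3) or extreme (4"). This is an intensity scale that defers to the appendix.
- **Appendix 4, pain at injection site.** Grade 1 is "Mild, no Rx required or analgesics for mild-moderate pain". Grade 2 is "Moderate requiring regular analgesics for mild-moderate pain or occasional analgesics for moderate-severe pain". Grade 3 is "Severe, repeated analgesics for moderate-sever pain". In the same table, grade 3 headache is "Severe; intractable; OR requiring repeated analgesics for moderate-severe pain".
- **Appendix 5, guide for local reactions.** The column headings pair each grade with mild, moderate, severe or extreme. The cells for pain in the injected muscle speak only of treatment at grades 1 to 3. Grade 1 is "No treatment or responds to paracetamol like treatment", grade 2 is regular need of paracetamol-type treatment, and grade 3 is regular need of strong painkillers.

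**The concern.** Intensity and analgesic use are different measurements. Some people with severe muscle pain take nothing, and others get by on paracetamol. A grading rule has to say which measurement governs when the two disagree. Here one text uses intensity, one uses both without saying how they combine, and one puts intensity in the heading and treatment in the cell.

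The grade 3 boundary decides whether a participant counts as an event in the primary safety comparison and towards the three-participant threshold. If the boundary depends on which text the grader follows, the recorded rate partly reflects the form and the participant's attitude to painkillers. The likely direction is under-recording, because the treatment-only wording can place severe pain at grade 1.

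**Working it through.** No figure in the plan is at issue, so the check is textual. It takes four participants, all with pain that they themselves call severe, through each definition.

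| Management of the severe pain | Section 4.1.1 | Appendix 4 row | Diary heading | Diary cell |
|---|---|---|---|---|
| Nothing taken | 3 | unresolved | 3 | 1 (3 if strong painkillers were needed but not taken) |
| Relieved by occasional paracetamol | 3 | unresolved | 3 | 1 |
| Not relieved by paracetamol, no strong painkillers taken | 3 | unresolved | 3 | not 1; 3 if strong painkillers count as needed |
| Repeated strong painkillers | 3 | 3 | 3 | 3 |

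**Why Appendix 4 is unresolved.** The comma in the grade 3 cell can be read in three ways.

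1. As AND: the first three participants lack the analgesic condition, and since their pain is neither mild nor moderate, no cell describes them.
2. As a label followed by a description: severe pain is grade 3 and the analgesic text only illustrates it.
3. As OR: severe pain is grade 3. But the grade 1 cell is punctuated in the same way, so on this reading untreated severe pain also meets grade 1, and a rule on which grade prevails is needed.

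The headache cell shows that the authors wrote OR where they meant alternatives. That makes its absence in the pain cell hard to interpret, but it does not prove AND.

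**Whether another rule settles it.**

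- The general scale at the head of Appendix 4 applies only to events without their own row. Pain has one.
- Section 4.1.1 gives a visit observation precedence over the diary only when both fall on the same day.
- The diary is filled in only on days without a clinic visit. After the one-hour observation in section 2.3.1, the schedule in section 2.6 puts the next visit about one week after each DNA dose (weeks 1, 5 and 9) and two weeks after each NYVAC dose (weeks 22 and 26, each with a window of one week either way). In the first days after injection the diary guide is therefore normally the grading source.
- The card asks participants to contact staff about grade 3 or 4 symptoms. An entry of grade 1 would not prompt that contact.

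**Size.** A figure would need the rate of severe pain in each group and the share managed without strong analgesics. The protocol gives neither. Pain is also only one part of an endpoint that includes cutaneous, systemic, other clinical and laboratory events, and discontinuations. No loss of power or change in the chance of a pause can be derived.

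**The case against.** The strongest reply is that the words are adequate for a sensible grader. Section 4.1.1 links the word severe to grade 3, the diary headings repeat it, and the treatment text can be taken as illustration. The diary's grade 3 cell speaks of strong painkillers being needed, which is not the same as taken. Its grade 1 cell requires a response to paracetamol if any was used. Treatment need appears elsewhere in the scale too: the grade 2 headache cell in Appendix 4 is worded almost as the pain cell is, and the diary headache row is also treatment-based. Investigators grade the safety endpoints, the Operational Sub-Group reviews them, and unresolved queries go to the TCC.

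Much of this stands, and it limits the point. A reader might infer that grade 3 requires severe pain and repeated analgesics together, so that severe pain managed otherwise fits no grade. That is only one reading of a comma. A reader might also infer that the diary carries no intensity words for pain; its column headings do.

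What does not fall away is the mismatch. The review steps help only if a discrepancy is noticed, and a self-recorded grade 1 gives little reason to query it. Reading the cells as illustration is reasonable, but the protocol does not say so.

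**Conclusion.** The point holds as an unreconciled definition. Two graders who both follow the protocol can give the same untreated or paracetamol-managed severe pain grade 1 or grade 3, and the difference decides whether it enters the primary safety endpoint and the section 7.7.2 count. Under-grading is possible and is the likelier direction of error. This rests on the diary being the usual source in the first days after injection, and on some participants with severe pain not using strong painkillers.

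It might be inferred that such pain certainly drops out of the endpoint, or that a stated amount of power is lost. The documents do not support either: intensity-based grading remains open under section 4.1.1 and the diary headings, and no rates are given. The defect is worth correcting because it sits on a primary endpoint and the correction is small.

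**What to change.** Reconcile section 4.1.1, the Appendix 4 pain row and the diary pain row so that one rule sets the grade, and state whether intensity alone is enough. One form already in the protocol is that of the grade 3 headache cell: severe in intensity, OR requiring repeated analgesics of the moderate-to-severe kind. If that form is chosen, word the grade 1 and 2 cells to match, say that the higher grade applies when intensity and treatment disagree, and make the diary cells agree with their headings.

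The cost is a wording change in one Appendix 4 row and one diary row, with a matching line in section 4.1.1. If intensity alone is made sufficient, the recorded grade 3 pain rate may rise somewhat, and with it the chance of reaching the three-participant review. This protocol version is dated April 2008 and enrolment was planned from early 2007, so some participants may already have been graded on the existing card. The date of any change should be recorded, so that pain grades before and after it can be told apart.

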#### **4.1.2 Systemic adverse events**

Temperature will be measured by the oral route prior to immunisation and one hour later by study personnel, and graded according to appendix 4. Participants will be given digital thermometers to record their temperature in the diary card on the evening of immunisation, and daily thereafter for 7 days, and if still raised, they will be advised to continue to monitor their temperature daily until it returns to normal. The temperature observed by the clinical team will be recorded on the case record forms for visits.

Chills, headache, nausea, vomiting, malaise and myalgia will be graded by the participants according to appendix 4, recorded in the diary card on the evening following immunisation and daily for 7 days, or until resolution of symptoms whichever is longer. On days where a visit coincides with the diary card, the clinical staff will collect the information directly and record it on the case record form, and this will take precedence over diary card entries in the analysis.

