| Vomiting                        | Less than 4 x a day or lasting less than 1 week                        | At least 4 x day or lasting 1 week or more                               | Unable to keep any food or fluids down                         | Hospitalisation     |

- Complete at approximately the same time every day ONLY on days that you are NOT going to clinic
- Fill in temperature and record the grade of other general reactions (use the table above as a guide)
- Add any comments regarding other symptoms
- Record any medication taken including over the counter medicines and anything taken to relieve local reactions
- Record the grade, or size in cm, of local reactions overleaf
- Please contact a member of the trials staff as soon as possible if you experience any symptoms of grade 3 or 4
- When the diary card is complete, please return it to a member of trials staff at your next visit

|                                                               | 12 hrs      | Day 1       | Day 2       | Day 3       | Day 4       | Day 5       | Day 6       | Day 7       |
|---------------------------------------------------------------|-------------|-------------|-------------|-------------|-------------|-------------|-------------|-------------|
| General Symptoms                                       |             |             |             |             |             |             |             |             |
| Date                                                   |             |             |             |             |             |             |             |             |
| Temperature °C                                         |             |             |             |             |             |             |             |             |
| Chills/rigors                                          |             |             |             |             |             |             |             |             |
| Malaise/ tiredness                                     |             |             |             |             |             |             |             |             |
| General muscle aches                                   |             |             |             |             |             |             |             |             |

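### Appendix 4 grades fever on temperature lasting more than 12 hours, but only isolated readings are collected, so one raised reading below 103°F (39.4°C) has no defined grade

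*Protocol*

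**What the plan says.** **The rule.** Protocol Appendix 4, Clinical parameters, heads the fever row "Oral>12 hours". Its °C bands are 37.7–38.9 (grade 1), 39.0–39.7 (grade 2), 39.8–40.5 (grade 3) and above 40.5 (grade 4). Grades 2 to 4 also have a peak-temperature alternative: "OR max temp of 103°F" for grade 2, "OR max temp of 103.5°F" for grade 3, and a peak above 105°F for grade 4. Grade 1 has none.

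**The data.** Section 4.1.2 states: "Temperature will be measured by the oral route prior to immunisation and one hour later by study personnel, and graded according to appendix 4". Participants then "record their temperature in the diary card on the evening of immunisation, and daily thereafter for 7 days". If the temperature is still raised they "continue to monitor their temperature daily until it returns to normal". The diary card (Appendix 5) has one temperature cell at 12 hours and one for each of Days 1 to 7, with the instruction "Complete at approximately the same time every day ONLY on days that you are NOT going to clinic". Neither place has a field for the start, end or duration of a fever.

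**Where the grade is used.** The primary safety parameters in Section 1.5.1 include "Grade 3 or above systemic adverse event (temperature, chills, headache, nausea, vomiting, malaise, and myalgia"). Grade 1 and 2 events are a secondary endpoint (Section 1.5.2). Section 8.3.2 tabulates solicited systemic events by maximum grade and immunisation timepoint.

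**The concern.** The grading rule needs a quantity that the protocol does not collect. A diary entry of 38.5°C or 39.2°C on one day falls inside a temperature band, but nothing on the form shows whether it lasted more than 12 hours, and below 103°F no other route leads to a grade.

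The protocol also applies the row in a way that the row does not allow. A reading one hour after injection cannot demonstrate a 12-hour fever, yet Section 4.1.2 has it graded by Appendix 4. A grader must either disregard the row heading or leave the reading ungraded, and the text does not say which.

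Grading is done by Clinical Investigators at several centres who know the allocation (Sections 1.2.1 and 8.2). If they settle the ambiguity differently, the fever counts in the Section 8.3.2 tables would partly reflect the grader.

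**Working it through.** No figure in the protocol can be reproduced for this point. The check compares the rule with the measurement schedule.

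**1. Which readings depend on duration?** Using °C = (°F − 32) × 5/9:

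- Grade 2 peak clause: (103 − 32) × 5/9 = 39.44°C.
- Grade 3 peak clause: (103.5 − 32) × 5/9 = 39.72°C.

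So 37.7–38.9°C reaches grade 1 only through the duration-qualified band, and 39.0 to about 39.4°C reaches grade 2 only through it. A reading of 39.5°C is 39.5 × 9/5 + 32 = 103.1°F and reaches grade 2 on its peak.

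**2. Is grade 3 in °C affected?** The lower edge is 39.8°C, which is 39.8 × 9/5 + 32 = 103.64°F. That already exceeds 103.5°F, so every reading in the °C grade 3 band qualifies without duration.

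**3. What can daily readings show?** Assume readings 24 hours apart, an unbroken fever of D hours, and a random start relative to the reading time.

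- P(at least one raised reading) = min(1, D/24)
- P(at least two raised readings) = max(0, min(1, (D − 24)/24))

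| D (hours) | at least one | at least two |
|---|---|---|
| 12 | 0.50 | 0 |
| 18 | 0.75 | 0 |
| 24 | 1.00 | 0 |
| 30 | 1.00 | 0.25 |
| 36 | 1.00 | 0.50 |
| 48 | 1.00 | 1.00 |

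A fever of 12 to 24 hours meets the rule but leaves at most one raised daily reading, which cannot prove it. A fever of 48 hours or more is always bracketed by two.

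**4. Do the two temperature scales agree?**

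| °C edge | converts to | table prints |
|---|---|---|
| 38.9 (top of grade 1) | 102.0°F | 101.5°F |
| 39.7 (top of grade 2) | 103.5°F | 102.9°F |
| 39.8 (bottom of grade 3) | 103.6°F | 103°F |

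They do not agree. A sustained 39.5°C (103.1°F) is grade 2 in °C and grade 3 in °F. The figure 103°F is both the grade 2 peak and the bottom of the grade 3 °F band.

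**The case against.** The strongest reply is that the protocol never says a raised reading of unproven duration is ungraded or excluded. Section 4.1.2 has single readings graded by Appendix 4, which suggests that graders may apply the bands directly. Section 2.3.2 keeps the team in contact until solicited events resolve and allows extra visits to clarify observations, so duration can be asked about. Events are validated before analysis (Section 7.3), and the Operational Sub-Group reviews the grades (Section 8.2). Both groups receive four immunisations under the same rule, and no bias between them is shown.

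Much of this stands. A reader might infer that most fevers below 103°F drop out of the results and that fever rates by regimen are understated. The documents do not support that. No text removes such readings, and the share affected depends on fever durations that the protocol does not give; it could be anything from 0% to 100%. A headcount could only come from an assumed rate of single-day fever (5–15% of 140 would be 7 to 21 participants), for which the protocol offers no basis.

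The 24-hour spacing is also not certain throughout. If the diary's Day 1 means 24 hours after injection, the first gap is about 12 hours. Two raised readings 12 hours apart would still sit on the edge of a criterion of more than 12 hours.

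The reply does not remove the contradiction. Contact and review can settle individual cases, but the written rule still does not fit a single reading. The general grading scale in Appendix 4 is for events not listed in its tables, and fever is listed.

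**Conclusion.** The concern holds in a limited form. As written, the fever row cannot be applied to an isolated reading of 37.7 to about 39.4°C, and Section 4.1.2, Appendix 4 and Appendix 5 contradict one another on how such a reading is handled. The possible harm is under-counting if the row is followed literally, or inconsistent grading between centres. It is confined to grade 1 and lower grade 2 fever in a secondary endpoint and descriptive tables, and its size cannot be derived from the protocol.

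A reader might also infer that this mismatch puts the primary safety endpoint at risk. In °C, the scale used on the diary card, it does not, because every grade 3 reading already meets the peak clause. In °F, a reading from 103°F to just under 103.5°F is grade 2 or grade 3 depending on unrecorded duration. That strip comes from the mismatched bands and is a reason to correct the whole row.

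The conclusion takes each peak clause to mean at or above the stated temperature. Only the table of detection probabilities relies on 24-hour spacing, an unbroken fever and a random start. This is a minor point, but cheap to correct.

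**What to change.** Reconcile Section 4.1.2, the Appendix 4 fever row and the Appendix 5 diary card. For the solicited-fever tables, grade on the highest oral temperature recorded after each immunisation, from diary or clinic, in °C and with no duration condition.

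Deleting the row heading alone is not enough. The 12-hour condition is what currently separates the sustained bands from the peak clauses. Without it, a single 103.2°F reading would meet both the grade 2 peak clause and the grade 3 °F band. The same edit must therefore reconcile the peak clauses and the °C and °F edges.

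Grade 3 also feeds the primary safety parameters (Section 1.5.1) and the discontinuation rules in Sections 5.4.1 and 7.7.2. The sponsor should check whether the revised row changes anything there; what those rules should be is not for this review to say.

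The cost is one table row and a clarifying sentence. No new data are needed, because the diary and case record forms hold the temperatures themselves and any existing grades can be re-derived. The downside is that brief fevers now count, so the grade 1–2 fever rate may be slightly higher.
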